**Fig 1 pone.0355623.g001:**

Timeline of stepped-wedge cluster randomized trial design (control, transition, and implementation periods).

### Study procedures

#### Pre-implementation phase.

The pre-implementation phase of the study will occur over a 12-month period prior to the intervention phase. During this phase, we will seek feedback from a variety of stakeholders to inform implementation strategy design through interviews, focus groups, and the development of a Community Advisory Board (CAB). Additionally, we will identify and engage with clinical champions at each PPIL health center to collaborate on recruitment of focus group and individual interview participants and design of local implementation strategies. The health center clinical champion will participate in regular meetings with the study team and help identify eligible staff and patients for the interviews.

For staff key informant interviews, we will recruit diverse staff members from the eight participating health centers with varying backgrounds, roles, and perspectives such as administrators, medical assistants, and providers. The interviews will focus on staff’s perspectives on barriers and facilitators to the implementation of the proposed strategies into clinical practice and any adaptation or resource considerations. Staff and providers will be recruited using informational flyers and in-person invitations by research staff and with the assistance of the health center’s clinical champion, PPIL’s Director of Research, and PPIL research assistants. Staff interested in participating will complete an eligibility screener via the informational flyer or otherwise contact the study team. Staff will be eligible to participate if they are (1) 18 years of age or older, (2) currently employed at a participating PPIL health center, (3) able to speak and understand English, and (4) willing and able to give consent. Interviews will be conducted by the study team either in-person at a health center or virtually via Zoom with audio recording only and no collection of personally identifiable information. Interviews will last approximately 30–60 minutes, and participants will receive a $50 incentive via physical or electronic gift card.

In addition to staff interviews, we will conduct interviews and focus groups with Black women seeking care at participating PPIL health centers. These interviews will be conducted to identify women’s preferences and needs regarding PrEP and to obtain specific feedback on the proposed implementation strategies and integration process. Active recruitment and enrollment of eligible patients will take place at each PPIL health center; staff from PPIL and members of the study team will recruit patients in the waiting area or lobby of each health center to inform them of the study. Passive recruitment will also occur via flyer distribution and postings, which will contain a QR code link to the eligibility screening survey and study team contact information. Patients will have the opportunity to complete the eligibility screening survey in person or remotely via the link. Patients will be eligible to participate if they are (1) 12 years of age or older; (2) Black/African American women; (3) a current patient of a participating PPIL health center, (4) HIV-negative or have unknown HIV status based on self-report, (5) able to speak and understand English, and (6) willing and able to give consent. Upon completion of the eligibility screening survey, participants will be presented with the choice to participate in a focus group or a key informant interview. Interviews will be conducted by the study team either in-person at a health center or virtually via Zoom with audio recording only and no collection of personally identifiable information. Interviews will last approximately 60 minutes, and participants will receive a $50 incentive via physical or electronic gift card.

To reflect the communities that we will be working with and to center the needs and perspectives of Black women, we will create a CAB during the pre-implementation phase, with representation from Black women of reproductive age and varied PrEP experience who seek care at PPIL. The CAB will consist of a facilitator who is a leader in PrEP and HIV advocacy in the Chicago area, as well as 6–8 community members who live in Cook County, Illinois and seek services at PPIL. The CAB will engage in a planning and advisory role throughout the study duration by guiding the study approach and ensuring that the implementation strategies are tailored appropriately for Black women. The CAB members will meet quarterly throughout the study duration. Each member will be compensated $100 per meeting.

#### Implementation and post-implementation phases.

All outcome data to be collected are part of existing routine EHR data collection at PPIL. PPIL Information Technology (IT) will create custom reports in the PPIL data warehouse to be built utilizing the existing data fields and a table of desired variables (Table 3).

**Table 3 pone.0355623.t003:** Requested electronic health record variables within limited data set.

Data domain	Brief description
Denominator/overall PrEP eligibility	Number of patients who are eligible to learn more about and receive PrEP according to study criteria: all patients 12 years or older, who are not living with HIV, and who have had a relevant medical encounter (e.g., family planning, sexual health care, primary care, etc.) during which PrEP could be prescribed *PrEP ineligibility: Patient is less than 12 years old or is medically unable to use PrEP (e.g., living with HIV) or attends a medical encounter during which PrEP is unlikely to be discussed or prescribed.
PrEP eligibility characteristics	STI screening history, risk factors, prior PrEP visits, and HPI for PrEP, visit date, visit type, location of care
Primary and secondary outcome measures	
PrEP initiation (i.e., initial prescription) – primary outcome	Proportion of Black women at each site who receive an initial prescription for PrEP (i.e., have not received a prescription for PrEP in the prior six months)
PrEP persistence (i.e., subsequent/refill prescription) – secondary outcome	Proportion of Black women at each site who receive a subsequent prescription of PrEP after initiating PrEP (i.e., refill initial prescription within six months)
Process measures	
HIV risk assessment	Proportion of eligible Black women who undergo HIV risk assessment at each site
PrEP education	Proportion of eligible Black women who receive PrEP education at each site
PrEP navigation	Proportion of eligible Black women who are referred to PrEP navigator at each site
Sociodemographic data/covariates	Gender identity, sex assigned at birth, sexual orientation, race, ethnicity, date of birth, gravidity, parity, annual income, preferred language, home zip code, marital status, disability status, HIV status, STI testing and diagnosis history within past year, location of care, prescription name(s) and duration(s)

PrEP: Pre-exposure Prophylaxis; STI: Sexually Transmitted Infection; HPI: History of Present Illness

Reports will be built to monitor (1) EHR alert consistency, (2) if PrEP is offered, (3) if PrEP is accepted or declined, and (4) among those who accept, if patient navigation is utilized and if PrEP is prescribed. These data will be collected at the health center level and during two phases: 1) the control, or baseline phase and 2) the intervention phase. The control and intervention phases are of variable length depending on step assignment (Fig 1). Implementation outcomes of each health center will be assessed at the midpoint and endpoint of the intervention period.

The initiation of PrEP prescriptions for eligible Black women (primary clinical outcome) will be measured using de-identified patient-level EHR data. Eligibility for inclusion in the outcome measures among patients will be determined based on study inclusion criteria such as patient’s age, biological sex and gender identity, and race. The primary outcome will be the proportion of eligible Black women at each health center who receive a prescription for PrEP during that month. The secondary outcome will be PrEP refills within six months, i.e., receipt of a PrEP prescription within six months of the index visit among those in the eligible population with a prior PrEP prescription. Finally, the total number of PrEP prescriptions among all patients in the control (baseline) and intervention periods will be analyzed to determine the impact of the implementation strategies on the entire PPIL patient population.

At approximately the midpoint of each site’s intervention period, key informant interviews including focus groups and interviews will be conducted with PPIL staff, clinicians, and women to assess implementation outcomes such as acceptability, feasibility, and fidelity over time. These interviews will elicit information related to the barriers and outcomes encountered during implementation. Procedures for recruitment and enrollment for these participants will mirror those of pre-implementation qualitative data collection completed as part of Aim 1. Data will be coded according to the RE-AIM constructs, with emerging themes identified and categorized by implementation outcome: acceptability, feasibility, and fidelity (Table 4). The usage of mixed methods in this study will be used to elaborate on quantitative RE-AIM findings with themes from qualitative data. Participant recruitment and data collection are expected to be completed by June and December 2028, respectively.

**Table 4 pone.0355623.t004:** RE-AIM outcomes.

RE-AIM dimension	Data source	Outcome
Reach	EHR	Percent of PrEP eligible women identified
Effectiveness	EHR	Percent of eligible women receiving PrEP prescription
Adoption	EHR	Percent of eligible women offered PrEP
Implementation	EHR Key informant interviews	Acceptability and feasibility of intervention as reported by staff, clinicians, and patients
Maintenance	EHR	Reach and implementation over time(Timeline: Months 13–60)

RE-AIM: Reach, Effectiveness, Adoption, Implementation, and Maintenance; EHR: Electronic Health Record; PrEP: Pre-exposure Prophylaxis

#### Sample size.

This study will be powered to determine whether there is a statistically significant difference in PrEP prescriptions among at-risk Black women defined as those with a positive STI test accessing family planning services between the intervention and control periods. We choose to use presenting to a family planning clinic and a positive STI test (gonorrhea, chlamydia, or syphilis) as eligibility to ensure patients at high risk for HIV acquisition are offered PrEP within the PPIL context, keeping in line with the CDC’s guidance to offer PrEP to patients at substantial risk of HIV acquisition. A power calculation was conducted based on a mixed effects effectiveness model with a random intercept for clinic and intervention and time as fixed effects. Assuming a baseline PrEP uptake of 1% and a conservative intraclass correlation coefficient (ICC) of 25%, a trial with 10 PrEP-eligible Black women per month (30 women per step) at each of the 8 clinics (8 steps) would allow us to detect an increase to 5% PrEP uptake (corresponding to an odds ratio of 5.21 for the intervention effect) in eligible Black women following the introduction of the intervention with >90% power at a two-sided alpha of 0.05. Our sample size provides almost 100% power for detecting a larger increase to 15% PrEP uptake (corresponding to an odds ratio of 17.47 for the intervention effect). Our sample size accounts for both the clustered nature of the design and the potential confounding effect of time. We used R software for power analysis.

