### Setting

EUPHORIA implementation strategies will be adapted and implemented in eight PPIL health centers (Table 2). All study sites are located within Cook County, Illinois, which is a priority jurisdiction of the CDC’s Ending the HIV Epidemic (EHE) initiative [24]. These sites were chosen due to their area’s heightened HIV burden as identified by the EHE initiative and the higher volume of PrEP-eligible Black women within their patient population. All participating PPIL health centers currently have low PrEP usage (<1%) among Black women who receive care at their sites. Additionally, these sites were selected due to their varied locations within Cook County and subsequently, varied contextual factors (e.g., prevalence rates of HIV and other STIs, economic hardship index scores, etc.). By adapting and implementing the proposed strategies in multiple distinct neighborhoods within Cook County, we aim to assess the consistency and discrepancy of implementation outcomes across sites, increasing applicability of findings to a broader range of settings through exploration of site-specific contextual elements.

**Table 2 pone.0355623.t002:** Participating health centers and corresponding patient volume in calendar year 2023.

Planned Parenthood of Illinois Health Center	Number of unique Patients	Volume of patients who are women	Volume of patients who are Black women
Heath Center 1	3,532	2,046 (57.9%)	224 (6.3%)
Health Center 2	4,732	2,889 (61.1%)	438 (9.3%)
Health Center 3	3,462	1,128 (32.6%)	224 (6.4%)
Health Center 4	4,611	870 (30.2%)	144 (3.1%)
Health Center 5	10,214	3,970 (38.8%)	502 (4.9%)
Health Center 6	3,849	2,584 (67.1%)	518 (13.5%)
Health Center 7	4,293	1,457 (33.9%)	217 (5.1%)
Health Center 8	2,838	857 (18.8%)	144 (5.1%)

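### The article defines the eligible population for the primary outcome in two incompatible ways, and the stated >90% power is attached to the one that Table 3 does not use

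*Protocol article*

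**What the plan says.** **Sample size section (Protocol article).** The power statement refers to a difference in PrEP prescriptions "among at-risk Black women defined as those with a positive STI test accessing family planning services". The next sentence makes the STI result an eligibility rule: "We choose to use presenting to a family planning clinic and a positive STI test (gonorrhea, chlamydia, or syphilis) as eligibility". The inputs are 10 eligible Black women per month (30 per step) at each of 8 clinics, baseline uptake 1%, ICC 25%, a rise to 5% (odds ratio 5.21), and power above 90% at two-sided alpha 0.05.

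**Table 3 (Implementation and post-implementation phases).** The denominator is "all patients 12 years or older, who are not living with HIV, and who have had a relevant medical encounter". The ineligibility note lists age under 12, being medically unable to use PrEP, and an encounter where PrEP is unlikely to come up. It does not list a negative or missing STI test. The primary outcome is "Proportion of Black women at each site who receive an initial prescription for PrEP". STI history appears only among the eligibility characteristics and the covariates.

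**Outcome text in the same section.** "The primary outcome will be the proportion of eligible Black women at each health center who receive a prescription for PrEP during that month". Inclusion in the outcome measures rests on "study inclusion criteria such as patient’s age, biological sex and gender identity, and race".

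**Quantitative data section.** The mixed model has a random site intercept and fixed effects for intervention and time interval. It is not restricted to STI-positive women.

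**Setting section.** The participating centers "currently have low PrEP usage (<1%) among Black women who receive care at their sites".

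**The concern.** The word eligible carries two explicit meanings in one article. One requires a positive gonorrhea, chlamydia or syphilis test; the other does not. The two populations can have different baseline rates, numbers per period and intervention effects, so they answer different questions.

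The power inputs also seem to come from both groups. The 10 women per month are STI-positive by the section's own definition. The 1% baseline resembles the figure below 1% that the Setting section gives for all Black women. The resemblance is loose, since one figure is current use and the other is uptake, but the article gives no baseline for STI-positive women.

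At stake is which population the primary effect describes, and whether the only power statement in the article belongs to it.

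**Working it through.** **1. Reproducing the plan's figures.**

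Odds ratios: (0.05/0.95)/(0.01/0.99) = 5.21 and (0.15/0.85)/(0.01/0.99) = 17.47. Both match.

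Power was computed by generalised least squares for a stepped wedge with a random site intercept and categorical time, on the probability scale. For each site:

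- V = diag[p(1−p)/n] + τ²J, where J is a matrix of ones and τ² = ICC/(1−ICC) × mean p(1−p)
- information = Σ Z′V⁻¹Z, where Z holds the period indicators and the intervention indicator
- power = Φ(|p1−p0|/SE − 1.96)

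Inputs from the article are 8 sites, one per step, n = 30 per site-step, ICC 0.25, and 27 months = 9 quarters. A schedule of 10 periods was also tried. With no quarter dropped and arm-specific binomial variance, 9 periods give SE = 0.0112 and power Φ(0.04/0.0112 − 1.96) ≈ 94.6%; 10 periods give 95.1%. A variance averaged over the two arms gives 88-90%. So the >90% reproduces for the population and inputs stated beside it.

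**2. Definitions side by side.**

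| Place | Positive STI test required? |
|---|---|
| Sample size section | Yes, as eligibility |
| Table 3, denominator and ineligibility note | No |
| Table 3, primary outcome | No |
| Outcome text | Not named; the list of criteria is open |
| Quantitative data section | No restriction |

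**3. Illustrative power in the Table 3 population.**

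Volume: the Black women in Table 2 sum to 224 + 438 + 224 + 144 + 502 + 518 + 217 + 144 = 2,411 per year, so 2,411/8/4 = 75.3 per site-quarter on average. Each site's own annual count divided by four was used (36 to about 130). This is an assumption. Table 2 counts unique patients per year, so the division may understate cell sizes if women return in several quarters.

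With baseline 1%, ICC 0.25 and each site's transition quarter dropped, the ranges below cover 9 or 10 periods, the position of the dropped quarter and the choice of variance:

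| Overall uptake under intervention | Power |
|---|---|
| 5% | 98% or more |
| 3% | about 69-78% |
| 2.6% | about 54-62% |

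On these inputs, 90% power needs overall uptake of about 3.5-4.0%.

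**4. Where 2.6% comes from.** The planned 30 STI-positive women per step against 75.3 Black women per site-quarter is 30/75.3 = 40%. If uptake rises from 1% to 5% in that share only, overall uptake is 1% + 4% × 0.40 = 2.6%. The 40% follows from the article's planning figures. It is not an observed positivity, and the article gives none.

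**The case against.** The strongest reply is that the STI rule in the Sample size section carries over to the eligible Black women of the outcome text. That text says "Eligibility for inclusion in the outcome measures among patients will be determined based on study inclusion criteria such as" age, sex, gender and race, so its list is open. On that reading the >90% does belong to the primary analysis, and Table 3 is the place that needs correcting. The reading is possible, but Table 3 states its denominator as following the study criteria and leaves the STI test out. The article does not say which definition governs.

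A second reply is that a wider population only adds women and therefore power. That holds if the effect stays the same size, and it may: Table 1 gives PrEP education to all Black women at each visit, and the provider training and EHR tools are clinic-wide. The 2.6% case assumes no effect at all in STI-negative women, so it is an unfavourable case and not a forecast.

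A third reply is that the full protocol or analysis plan may name one population. It may, and for that reason the point is limited to what the article states. An unseen document cannot make both definitions true.

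**Conclusion.** The contradiction stands on the text alone: the article does not fix one eligible population for the primary outcome, and its power statement is not tied to the outcome as Table 3 defines it. That conclusion does not depend on any volume or positivity.

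The consequence for power is conditional. In the Table 3 population it runs from 98% or more at 5% overall uptake to about 54-62% at 2.6%, under the assumptions listed with the calculation.

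A reader might infer more, and the article does not support it:

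- **That the trial is underpowered.** The mismatch alone does not show this; the answer turns on how far women without a positive test respond.
- **That power could be far lower because few women test positive.** This needs a positivity figure that the article does not give.
- **That the package would change who is tested and so shift the STI-positive group at go-live.** No strategy in Table 1 is STI testing, so this is speculation.
- **That the population would be chosen after seeing results.** Nothing in the article shows this.

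**What to change.** Name one primary analysis population, in the same words, in Table 3, the outcome text and the Sample size section. Restate for it the baseline rate, the monthly number per clinic, and the power or detectable difference, with transition quarters excluded as the Study design section requires.

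- **If the Table 3 population is primary:** its membership does not depend on who was tested. Report STI-positive women as a pre-specified subgroup.
- **If STI-positive women are primary:** add that restriction to Table 3 and the outcome text, and take the baseline from that group.

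The detectable difference should come from the team's own re-run; the figures here are illustrative and depend on the model, the ICC and the volumes. The change concerns the analysis denominator only, not who is offered PrEP.

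The cost is wording in three places and one power re-run. The downside is that the stated detectable effect, or the population that it refers to, may change.

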#### Informed consent.

A waiver of parental permission was provided for Aim 1 and Aim 3 of this study. Under the statutory authority of Illinois State Law (410 ILCS 210), minors in this specific age category (12–17, inclusive) may consent on their own authority to participate in this research study.

No individual patient consent or recruitment is required for activities related to Aim 2 of this system-level, clinic-level health service delivery intervention, and therefore outcomes may be obtained through routinely collected de-identified data from the PPIL EHR.

### Analysis

#### Qualitative data.

Data collected from focus groups and key stakeholder interviews with patients (see S1 File) and staff (see S2 File) during the pre-implementation, implementation, and post-implementation phases will be thematically coded according to CFIR and RE-AIM constructs using Dedoose software. Emerging themes will be identified and categorized by construct and/or implementation outcome and used to create a codebook with unique definitions and examples for each code. The data will be coded by at least two independent coders then discussed to resolve coding discrepancies and to maintain high inter-rater reliability (80% agreement). During pre-implementation, emerging themes will be identified and categorized as important considerations for implementation planning, highlighting key content and contextual modifications; these adaptations may include refining to make intervention strategies more appropriate or applicable, adding/removing/substituting intervention components, or adjusting pacing. For instance, adaptations may include adjusting the frequency, duration, and content of the provider training sessions. Similarly, modifications to EHR optimization will aim to enhance existing processes for PrEP screening, prescribing, and navigation. Patients will also be asked about their experiences and perceptions of existing PrEP educational materials during interviews to guide updates that reflect patient preferences and improve relevance for various populations.

During implementation and post-implementation, emerging themes will provide feedback on the strengths and weaknesses of the intervention based on the RE-AIM framework to improve future implementations and assess implementation processes. Additionally, the Framework for Reporting Adaptations and Modifications (FRAME) will be used to facilitate comprehensive documentation of adaptations made to illustrate significant mechanisms and processes in implementation [23].

